### 2.5. Intervention

The FOODLIT-Trial is an online-enabled intervention to promote food literacy and food sustainability practices delivered with digital evidence-based resources in multiple formats, based on theoretically informed behaviour change approaches, and made available through mobile phone, tablet, and computer. The intervention will include weekly reminders for participants to evaluate their food-related knowledge, competencies, and behaviours, and assess related psychological mechanisms associated with behaviour change. Experimental and comparison group specifications are described below.

#### 2.5.1. Experimental Group

Participants allocated to the EG will receive weekly information concerning a specific theme through digital sources such as videos, infographics, and web-directed links. The 11-week intervention is designed according to (a) the food-related knowledge, competencies, and behaviours belonging to the core of the FLW conceptual and empirical model, and (b) the psychological mechanisms within the HAPA framework. As shown in Table 1, each week entails not only a set of skills, behaviours, and/or mechanisms that feature the above mentioned theoretical and empirical frames, but also a customised, well-defined, and identifiable technique from BCCT to prompt participants’ food-related behaviour change.

Participants in the EG will receive weekly (A) evidence-based and customised information related to a specific skill, behaviour, and/or mechanism, from sources such as national and international guidelines—namely, the Portuguese Directorate-General for Health and the EAT-Lancet Commission on Food, Planet, Health; (B) designated tasks based on each behaviour change technique and related to the week’s thematic; (C) a short introductory video, featuring the research coordinator, briefly mentioning the week’s thematic and alerting to the week’s assessment; (D) notifications reminding the need to respond to the week’s questionnaire (two days before the end of the week and the day of the due date for questionnaire response) and the corresponding link leading to the week’s questionnaire. All materials, except for the weekly questionnaires, will be stored in a purposely created website, allowing for participants to revisit previous weeks’ resources (if desired).

Shown in Table 2A is two-week example of (A) a customised infographic, (B) its associated task based on a behaviour change strategy, and (C) its corresponding items.

#### 2.5.2. Comparison Group

Participants allocated to the active CG will receive a single-time and non-customised delivery of the same food-related national and international guidelines. There will be no theoretically informed approach and no behaviour change techniques, and the delivered content will generically regard nutritious eating and food-related habits. No digital presence of the research coordinator will be featured to the CG (that is, no weekly introductory videos will be sent to this cohort). Additionally, to the (A) single-time (but non-customised) delivery of informative guidelines from the same entities, the CG will receive (D) the identical notifications serving as reminders for the weekly questionnaires (identical to the questionnaires delivered to the EG). Similarly to the EG, the guidelines will be stored in a specifically designed website, providing for uninterrupted access.

### 2.6. Adherence and Strategies to Minimise Drop-Out

To encourage intervention adherence and engagement, weekly reminders will be sent to participants of both EG and CG via email and/or WhatsApp. At the beginning of each week, the reminder will be sent via WhatsApp, notifying participants that a new week of FOOLIT-Trial is starting and that the weekly welcoming email was sent; for the EG, a link enabling the access to the week’s resources (A, B, and C) will be featured, while CG participants will be reminded of the access to where guidelines are stored (non-customised A). Two days before the end of each week, an email will be sent in the morning with the link leading to the week’s questionnaire; a notification through WhatsApp will be delivered later that day reminding that the link for questionnaire response is already available. At the due date for the weekly response, a final reminder will be sent through WhatsApp, indicating that the questionnaire will be available until the end of that day.

Additionally, as a strategy to minimise drop-out and to prompt continuous engagement, compensation will be featured within the FOODLIT-Trial. Compensation will entail the following randomised allocations of gift cards to participants for grocery shopping: (i) one gift card at the end of the 11-week intervention (with a credit of 50 EUR), (ii) a gift card at the end of the first and second follow-up (T2 and T3; a total of two gift cards with a credit of 25 EUR each), and (iii) two gift cards at the end of the last follow-up (T4; each gift card with a credit of 50 EUR).

### 2.7. Outcomes

#### 2.7.1. Primary Outcome Measure

Considering FOODLIT-Trial’s first aim, the primary outcome to be assessed is food literacy. Food-related knowledge, competencies, and behaviours will be assessed with the FOODLIT-Tool [17] at baseline (T0), during the 11-week intervention (with the items distributed across the theme for the week; Table 1), post-intervention (T1), and at all follow-ups (T2, T3, and T4). These longitudinal assessments will evaluate participants’ food literacy according to the five dimensions portrayed in the instrument (Culinary Competencies, Production and Quality, Selection and Planning, Environmentally Safe, and Origin) and based on the FLW [16]. These include (i) theoretical knowledge, such as knowing various types of food preservation suitable to different foods (item 10); (ii) practical competencies, as interpreting food labels to select adequate foods (item 19); and (iii) food habits and behaviours, such as eating foods according to their seasonality (item 22). All items are assessed with a four-point Likert-type response scale, concerning either frequency (0—*never*; 1—*sometimes*; 2—*frequently*; 3—*always*) or agreement (0—*completely disagree*; 1—*disagree*; 2—*agree*; 3—*completely agree*).

#### 2.7.2. Secondary Outcome Measure

Aiming to explore intervention performance, FOODLIT-Trial’s second aim is to evaluate which psychological mechanisms efficaciously predict change in participants’ food literacy. To achieve this objective, psychological mechanisms derived from the HAPA—including risk perception, outcome expectancies, self-efficacy, planning, and action control—will also be assessed at similar time points (from T0 to T4). All measures to evaluate HAPA constructs are adapted from Sniehotta, Scholz, and Schwarzer [59] and are specific to food literacy, depicting eating according to one’s needs as the intended behaviour. All items are also assessed with four-point Likert-type response scales, regarding agreement (0—*totally disagree*; 1—*disagree*; 2—*agree*; 3—*totally agree*) and possibility (0—*very unlikely*; 1—*unlikely*; 2—*likely*; 3—*very likely*).

## 3. Statistical Analyses

### 3.1. Randomisation Check, Drop-Out Analyses, and Intention to Treat

A randomisation check will address equal distributions of all baseline measures of all primary and secondary outcomes and covariates across conditions using multivariate analyses of variance interval–scale data, and chi-square tests for nominal and ordinal-scale data. Analyses will be carried out in an intention-to-treat manner, accounting for missing values using the full information maximum likelihood approach [60]. Drop-out analyses will test baseline differences between continuers and non-continuers in all variables using t-tests, chi-square tests, or logistic regression.

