### 2.3. Participants and Recruitment

Considering its web-based format, FOODLIT-Trial’s potential participants will represent a sample of convenience and snowballing, and will be reached and enlisted through online sources. Online reach out will be made by using both advertisements in social media websites according to the researcher’s network (Instagram and Facebook, Meta Platforms: Cambridge, MA, USA) and a developed website for participants’ enrolment. During the recruitment stage, potential participants will be informed that trial participation will entail compensation in order to acknowledge their time and effort dedicated to the study.

An a priori power analysis was conducted with G*Power (v. 3.1), and a minimum sample size of 28 was necessary in order to detect a medium effect size (Cohen’s d = 0.50) at the 5% level of significance with 95% power, with the assumption of the non-violation of sphericity (non-sphericity correction ε = 1) considering the trial’s repeated-measures design. Given a potential attrition rate of 50% due to the digital nature of the trial, its duration, and required weekly assessments, a minimum of 56 participants will be recruited.

Participants for the FOODLIT-Trial must (i) be adults aged 18 years or older, (ii) be able to understand and read Portuguese, (iii) have availability to engage in the 11-week trial, and have internet access that allows for their engagement, (iv) be responsible for, at least, one out of four tasks in their food routine (encompassing choice and decision, selection and acquisition, preparation, and cooking, according to [18]). Potentially eligible participants will be invited to the trial through an online information sheet, and will be provided with the consent form; if eligible, the baseline questionnaire (T0) will be made available and delivered online. Additionally, all participants will be asked to complete a sociodemographic questionnaire aiming to collect self-reported data concerning sociodemographic and health-related characteristics (e.g., sex, age, educational level, diagnosed diseases, height, weight).

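### With 50% attrition expected, the T0–T4 likelihood analysis leaves out weekly outcome scores collected in both arms; the effect may be biased if experimental-arm loss depends on in-trial response

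*Protocol article*

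**What the plan says.** - **Expected loss.** Section 2.3 gives its reasons and a rate: "Given a potential attrition rate of 50% due to the digital nature of the trial, its duration, and required weekly assessments". It inflates accordingly: "a minimum sample size of 28 was necessary" becomes "a minimum of 56 participants will be recruited". The 50% is not split by arm or by time.
- **Weekly outcome data.** Section 2.7.1 lists, among the assessment times of the primary outcome, "during the 11-week intervention (with the items distributed across the theme for the week; Table 1"). Section 2.5.2 says the comparison group's weekly questionnaires are "identical to the questionnaires delivered to the EG".
- **Effect model.** Section 3.2 fits linear two-level models to T0, T1, T2, T3 and T4, with a time by condition interaction and covariates. The weekly scores have no role.
- **Missing values.** Section 3.1 plans an intention-to-treat analysis, "accounting for missing values using the full information maximum likelihood approach". No auxiliary variables are named.
- **Drop-out check.** Section 3.1: "Drop-out analyses will test baseline differences between continuers and non-continuers in all variables", by t-tests, chi-square tests or logistic regression. Arm is not mentioned.

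**The concern.** Full information maximum likelihood is valid when drop-out depends only on values that are in the model. For a participant who leaves before T1, those values are arm, covariates and T0. How the person was doing in weeks 1 to 11 is not among them, although the trial measures it.

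The arms ask different things of people. Sections 2.5.1 and 2.5.2 set weekly customised material, tasks and videos against a single delivery of guidelines. Leaving because the tasks are not helping is therefore a plausible mechanism mainly in the experimental arm. If it operates there and not, or less, in the comparison arm, those who stay in the experimental arm are better responders than their T0 scores predict. The estimate would then drift upward from the effect in everyone randomised.

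**Working it through.** **1. The plan's own figure.** 28 / (1 − 0.5) = 56, which reproduces. At 1:1 that is 28 per arm. The 28 itself depends on a repeated-measures correlation that the article does not state, and it does not bear on this point.

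**2. What the weekly data contain (Table 1).** FOODLIT-Tool items by week: week 2, three; week 3, three; week 4, two; week 5, two; week 7, four; week 8, three; week 9, four; week 10, three. Sum: 3+3+2+2+4+3+4+3 = 24. Each is asked once. Items 6 and 7 appear in no week. Origin is asked only in week 2, Production and Quality only in week 9. Weeks 1, 6 and 11 carry HAPA items.

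**3. Which loss patterns cause bias.** Simulation with no true effect. The assumptions are not from the documents: drop-out happens before T1, and the baseline SD is 1.

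| Loss pattern | Drop-out, experimental v comparison | Bias, T0 conditioned within arm | Bias at T4, two-level model |
|---|---|---|---|
| Random within arm | 60% v 40% | 0.00 | −0.01 |
| Experimental arm depends on T0 | 58% v 40% | 0.00 | −0.03 |
| Experimental arm depends on weekly score | 57% v 40% | 0.32 | 0.26 |
| Both arms depend equally on weekly score | 50% v 50% | 0.00 | 0.04 |

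The simulation error of the last column is about 0.02. In the last row the same model on complete data already gave 0.0023 × 11.5 months = 0.03, so loss adds about 0.01. Only the third pattern does harm.

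**4. How the size varies.** Let u and e be independent with variance 0.5 each. T0 = u + e, later scores = u + r + e, weekly summary W = u + r + noise (variance 0.3). P(drop) = expit(−slope × W) in the experimental arm and 0.5 in the comparison arm, so about 50% are lost in each. Bias using T0 only:

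| Slope | SD of r = 0.25 | 0.50 | 0.75 |
|---|---|---|---|
| 0.5 | 0.08 | 0.12 | 0.19 |
| 1.0 | 0.14 | 0.22 | 0.33 |
| 1.5 | 0.18 | 0.28 | 0.43 |

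Adding W brings every cell to between −0.005 and 0.002. That near-zero result is built in, because W is seen for everyone and is the only driver of loss.

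**5. A more realistic version.** With loss week by week, and only the weekly scores seen before leaving, T0-only bias was 0.03 to 0.24 SD. Adding a single running weekly mean left −0.10 to 0.00, with no loss of precision at N = 56. The correction is real but inexact and can overshoot; the remainder depends on the assumed loss pattern.

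**6. Would the planned check see it?** At N = 56, the share of trials in which the pooled T0 comparison of continuers and non-continuers was significant:

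- harmful pattern (third row): 16%
- harmless pattern with equal dependence in both arms: 51%
- random loss: 6%

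So the check signals the harmless pattern more often than the harmful one. Its power for a 0.5 SD baseline difference, 28 v 28, is 45%.

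Comparing drop-out between arms does not solve this. A chi-square test was significant in 23% of trials under the harmful pattern, has about 32% power for 60% v 40%, and sees nothing if the rates are equal. An arm by baseline test with 14 per cell has SE = √(4/14) = 0.535. For a difference of 0.5 SD, z = 0.5/0.535 = 0.935 and power is about P(Z > 1.96 − 0.935) = 15%.

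**The case against.** **A condensed article leaves details to an analysis plan.** Auxiliary variables and sensitivity analyses often sit there, and nothing forbids them here. This stands in part, and it is why the point is not graded higher. But the article itself fixes the model's time points, the missing-data method and the drop-out check, and these leave out data that it assigns to the primary outcome.

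**The harmful pattern is speculative.** Digital format, duration and weekly questionnaires, the reasons given for attrition, are common to both arms. This stands: the mechanism is plausible because the arms differ in tasks, but it is not documented.

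**The larger figures are worst cases.** They put all 50% of loss before T1, although some will fall later and those people contribute T1. They also make comparison-arm loss random. In a related data model with bias of 0.17 to 0.28 under those conditions, 25% loss before T1 gave 0.08 to 0.15. Half-strength dependence in the comparison arm gave 0.08 to 0.12. This stands, and the range of 0.03 to 0.24 is the fairer one.

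**Stronger readings that the article does not support.** A reader might infer that selective or unequal loss as such biases the effect. It does not, because the model conditions on arm and on observed T0–T4 scores. A reader might also infer that the drop-out check ignores arm and that loss would go unseen. The text is silent on arm; testing all variables, with logistic regression among the methods, does not exclude it. The commitment to CONSORT means that losses by arm will be shown, although counts do not reveal who left within an arm.

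**Conclusion.** The point holds as a conditional one. The plan expects heavy loss, collects primary-outcome items in both arms during a period when part of that loss is likely, and then fits a model without them. If experimental-arm loss depends on in-trial response differently from comparison-arm loss, the time by condition effect may be biased by about 0.03 to 0.24 SD, and the planned baseline check would usually not reveal it. That range rests on assumed loss patterns, response variability and a true null; none of these comes from the article, and the bias may be nil. Severity is low to moderate: a cheap improvement to a standard method, not an error that invalidates the analysis.

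**What to change.** 1. **Auxiliary variable.** Include one parsimonious summary of the weekly FOODLIT-Tool responses from both arms, for example a running mean of the items answered so far, in the full information maximum likelihood step or in a multiple-imputation model. Do not enter five dimension scores and eight HAPA scores separately: 5 + 8 = 13 auxiliaries are too many for 56 participants.
2. **Sensitivity analysis.** Add one delta-adjusted analysis in which outcomes of experimental-arm dropouts are shifted toward the comparison-arm mean, and report the shift at which the conclusion changes.
3. **Description.** Report drop-out by arm at each time point. This is useful but has low power at N = 56 and is not the main remedy.

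**Cost.** Analysis work only; no new data and no change in design. The downside is that the weekly items are a one-pass, partial score without items 6 and 7, and early leavers have answered few of them (three by the end of week 2, six by the end of week 3). The correction is only partial for those people, which is why the delta analysis is needed beside it.

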### 3.2. Hypotheses Tests for Intervention Effects

Linear two-level models with five time points (T0, T1, T2, T3, T4; within-level) nested in participants (between-level) will be computed. For each outcome measure, time (linear day trend, centred at 0) x experimental condition (0 = comparison condition; 1 = intervention condition) interactions will be estimated. Moreover, grand-mean centred covariates (e.g., sex, age) will be added as between-level predictors. The linear time trend and the linear time trend x experimental condition interaction will be modelled as fixed effects.

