## 2. Methods and Analysis

### 2.1. Trial Design

The FOODLIT-Trial is a two-arm (allocation ratio 1:1), parallel, experimental, and single-blinded randomised controlled trial for Portuguese adults (Figure 1). The web-based intervention is delivered over 11 weeks, where each week is themed with content either according to the FLW framework or to the HAPA model.

In conformity to the week’s thematic, each ability, skill, and behaviour is matched with a behavioural change strategy to facilitate its implementation [55]. All measures will be assessed at five time points: baseline (T0), to measure baseline characteristics, pre-intervention, before randomised allocation, and prior to the trial’s first week; post-intervention (T1); one week after the 11-week intervention delivery; and at follow-up times 3, 6, and 9 months after the intervention (T2, T3, and T4, respectively).

This protocol adheres to the Consolidated Standards of Reporting Trials [56] guidelines for randomised controlled trials.

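### The plan treats time and time x condition as fixed effects and names no random slope; if participants' slopes differ, the primary test is too liberal, by an amount the article does not let us fix

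*Protocol article*

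**What the plan says.** Section 3.2 of the protocol article sets the structure: "Linear two-level models with five time points (T0, T1, T2, T3, T4; within-level) nested in participants (between-level) will be computed". For each outcome, the term that carries the intervention effect is given as "time (linear day trend, centred at 0) x experimental condition (0 = comparison condition; 1 = intervention condition) interactions will be estimated". Covariates enter at the between level. On the handling of time, the section says: "The linear time trend and the linear time trend x experimental condition interaction will be modelled as fixed effects".

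Neither section 3.1 nor section 3.2 mentions a random slope, a residual covariance structure or a standard-error estimator. Section 3.1 adds intention to treat with full information maximum likelihood for missing values.

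Section 2.1 describes a two-arm trial with 1:1 allocation. It places T1 one week after the 11-week delivery, and T2 to T4 at 3, 6 and 9 months after the intervention. Section 2.3 gives "a minimum sample size of 28 was necessary" and 56 to be recruited, with sphericity assumed for the sample-size calculation ("with the assumption of the non-violation of sphericity (non-sphericity correction ε = 1) considering the trial’s repeated-measures design").

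**The concern.** Condition varies between participants and time varies within them, so the primary effect is a cross-level interaction. Its true sampling variance contains the variation between people in their own slopes. A model with a random intercept and a common slope per arm leaves that component out. It implies the same correlation between every pair of visits and estimates the slope's uncertainty from the pooled within-person scatter.

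Over roughly a year of follow-up it is plausible that people change at different rates, or that neighbouring visits agree more closely than distant ones. The second aim looks for psychological mechanisms that predict change, which also suggests that change is not expected to be uniform. In either case the p-value for the primary hypothesis is too small and its confidence interval too narrow. The direction of the error is known; its size is not.

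**Working it through.** **Inputs from the article.** Five occasions; 1:1 allocation; 5% level (two-sided assumed, as sidedness is not stated); 28 participants after attrition and 56 recruited, where 28/(1 - 0.5) = 56. Converting months to weeks puts the visits at about weeks 0, 12, 24, 37 and 50.

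**Inputs assumed, because the article gives none.** Between-person slope variance tau^2 and residual variance sigma^2, or alternatively a serial correlation.

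**Time spread.** The mean week is 24.6, so Sxx = 605.16 + 158.76 + 0.36 + 153.76 + 645.16 = 1563.2.

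**Variance ratio.** Let k = tau^2 x Sxx / sigma^2. Slope reliability is R = k/(1 + k).
- The true variance of one person's fitted slope is (sigma^2/Sxx)(1 + k).
- Five visits leave four within-person contrasts. One is the linear slope, with variance sigma^2(1 + k); the other three have variance sigma^2. The random-intercept model pools them to sigma^2(1 + k/4), so it believes the slope variance is (sigma^2/Sxx)(1 + k/4).
- True/model variance is therefore (1 + k)/(1 + k/4), and the type I error is 2 x [1 - Phi(1.96/sqrt(ratio))].

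The nominal figure is reproduced first: k = 0 gives ratio 1 and 5.0%. The rest follow:

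| R | k | ratio | type I error | SD of 50-week change, in residual SDs |
|---|---|---|---|---|
| 0 | 0 | 1.00 | 5.0% | 0 |
| 0.1 | 0.111 | 1.081 | 5.9% | 0.42 |
| 0.2 | 0.25 | 1.176 | 7.1% | 0.63 |
| 0.33 | 0.493 | 1.329 | 8.9% | 0.89 |
| 0.5 | 1 | 1.60 | 12.1% | 1.27 |
| 0.67 | 2.03 | 2.01 | 16.7% | 1.80 |
| 0.76 | 3.17 | 2.33 | 19.9% | 2.25 |

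The last column is 50 x sqrt(k/1563.2). The ratio cannot exceed 4, which caps the error at about 33%. At R = 0.5 the interval is too narrow by 1 - 1/sqrt(1.6), about 21%.

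**Simulation check, random intercept only** (REML fits, 600 runs per setting, 1.96 cut-off, no intervention effect):

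| R | N = 28, complete | N = 56, 50% dropout |
|---|---|---|
| 0 | 4.5% | 6.0% |
| 0.3 | 8.0% | 11.0% |
| 0.5 | 12.8% | 13.5% |
| 0.7 | 18.5% | 17.5% |
| 0.8 | 21.7% | 25.7% |

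With a random slope added (N = 56, 50% dropout, 200 runs each), the error was 4% at R = 0.5 and 6% at R = 0.8. Simulation error is about 1-3 points with 600 runs and larger with 200, so both are compatible with 5%.

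**Serial correlation instead of random slopes.** The same comparison, true against model variance of the slope, was made in large samples at days 0, 84, 168, 259 and 351, with correlation decaying per 12 weeks:
- no independent measurement error: 13.3% at a correlation of 0.5 and 17.1% at 0.7;
- independent error with the same variance as the serial part: 8.5% and 9.1%;
- independent error at 70% of the two combined: about 7% in both cases.

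**The case against.** The strongest reply is that the article does not say what a reader might take from it. In a random-slope model the mean trend and the cross-level interaction are fixed effects too, so the sentence is compatible with a random slope. The article does not expressly exclude one, and it does not mention a random intercept either. An autoregressive residual or robust standard errors could also accompany fixed time, and a condensed article may leave such detail to the analysis plan. This stands in part: the fixed-slope model is an inference. It is still the natural one, because the section chooses to say how time is modelled and names only fixed effects.

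A reader might also infer that the plan's type I error is 9-20%, or that false claims rise two- to four-fold. The documents do not support that as an unconditional statement. The range corresponds to slope reliabilities of about 0.33 to 0.76 and leaves out the milder cases of 5-7%. Reaching 20% needs a between-person SD of the 50-week change of about 2.2 residual SDs, for which the article gives no basis. Self-reported four-point items may well carry much independent error, which pulls the serial-correlation figures down towards 7-9%.

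The sphericity assumption in section 2.3 does not answer the concern. It is a planning input and does not protect the test if it fails.

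**Conclusion.** The point holds in conditional form. As naturally read, section 3.2 describes a random-intercept model with a common slope per arm. Its time x condition test keeps the 5% level only if slopes are parallel within arm and correlation between visits is constant. Otherwise it is anti-conservative: mildly so with small slope heterogeneity, and more than double the nominal level from a slope reliability of about 0.4-0.5 upwards (10.1% at 0.4, 12.1% at 0.5). Under serial correlation the error runs from roughly 7% to 17%, depending on the share of independent measurement error.

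These figures rest on assumed variances, model-based standard errors and independent residuals; the article fixes none of the three. Since the choice governs the primary hypothesis and the remedy is cheap, this should be fixed, but the article does not show that the test is badly inflated.

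**What to change.** In section 3.2, keep the mean time trend and the time x condition interaction as fixed effects. Add a participant-level random slope for time with intercept-slope covariance, and state small-sample degrees of freedom (Kenward-Roger or Satterthwaite). Prespecify a fallback if that model does not converge: an autoregressive residual structure, or cluster-robust standard errors with a small-sample correction. Do not fall back to the random intercept alone. If a random slope is already intended, one sentence saying so settles the point.

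The cost is one line of model specification, somewhat wider confidence intervals, and possible convergence work with 28 to 56 participants. If slopes prove to be parallel, little is lost.
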